### Safety Outcomes

The safety outcomes of the investigational medication were assessed at T0, T1, T2, T3, and T4 by considering the following:

Measurement of vital signs: heart rate, blood pressure, temperature, and respirationLaboratory tests: blood routine, stool routine, and urine routineLiver function tests: alanine aminotransferase, aspartate aminotransferase, and bilirubinRenal function tests: urea nitrogen and creatinineElectrocardiogram

### Adverse Events

All AEs will be carefully documented, including the start and end dates, severity, relationship to the study drug, and patients’ continued involvement in the study. Any serious AE will be promptly reported to the research ethics committee within 24 hours. If an AE occurs, the patient will be advised to discontinue the use of the decoction, and the researchers will evaluate whether it is related to the formulation. Emergency safety measures will be implemented, if necessary, to ensure the well-being of patients. Persistence of AEs will be monitored until their resolution. Please note that AEs are not the complications clearly related to AP, such as acute respiratory distress syndrome, abdominal compartment syndrome, and acute kidney injury.

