**Objective:**

This study aims to evaluate the efficacy and safety of DaXianXiong decoction in preventing AP from progressing to SAP, assessing its impact on SAP incidence, clinical severity scores, inflammation markers, and gastrointestinal function, and providing evidence for AP management.

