### Outcome Measures

The outcome measures will be determined at various time points throughout the study, including baseline (T0, before treatment), 24 hours after the final treatment (T1, end point 1), 3 days after the final treatment (T2, end point 2), 7 days after the final treatment (T3, end point 3), and 28 days after the final treatment (T4, final end point). The data collection and assessment schedule are listed in Table 2.

**Table 2 table2:** The data collection and assessment schedule.

Assessments		Study period				Follow-up		
		Enrollment and allocation (T0)	Intervention (48 hours)	Primary end point (T1)	T2		T3	T4

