**Intervention**								
	Intervention group		✓					
	Placebo group		✓					
**Assessment**s								
	Incidence of SAP^a^			✓	✓		✓	✓
	Modified Marshall score	✓		✓	✓		✓	✓
	Modified CTSI^b^	✓		✓	✓		✓	✓
	APACHE II^c^ score	✓		✓	✓		✓	✓
	C-reactive protein	✓		✓	✓		✓	✓
	IL^d^-1	✓		✓	✓		✓	✓
	IL-4	✓		✓	✓		✓	✓
	IL-6	✓		✓	✓		✓	✓
	IL-8	✓		✓	✓		✓	✓
	IL-10	✓		✓	✓		✓	✓
	TNF^e^-α	✓		✓	✓		✓	✓
	Safety outcomes	✓		✓				
	Hospitalization							✓
	Survival							✓

^a^SAP: severe acute pancreatitis.

^b^CTSI: computed tomography severity index.

^c^APACHE II: Acute Physiology and Chronic Health Evaluation II.

^d^IL: interleukin.

^e^TNF: tumor necrosis factor.

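### The adverse-event rule sets aside complications attributed to pancreatitis before drug causality is judged, and the text and Table 2 disagree on safety assessment after T1

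*Protocol article*

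**What the plan says.** Safety stands beside efficacy in the Objective of the protocol article: "This study aims to evaluate the efficacy and safety of DaXianXiong decoction".

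The Adverse Events section provides for every AE to be documented, including its severity and its relationship to the study drug, and for AEs to be followed until they resolve. Two steps apply once an event is an AE or a serious AE: "If an AE occurs, the patient will be advised to discontinue the use of the decoction, and the researchers will evaluate whether it is related", and "Any serious AE will be promptly reported to the research ethics committee within 24 hours". The section closes with a boundary: "AEs are not the complications clearly related to AP, such as acute respiratory distress syndrome, abdominal compartment syndrome, and acute kidney injury". It does not say who decides that a complication falls on the far side of that boundary, by what criteria, or whether the decision is made blind to arm.

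On timing, the Safety Outcomes section says: "The safety outcomes of the investigational medication were assessed at T0, T1, T2, T3, and T4". It then lists vital signs, routine blood, stool and urine tests, liver and renal function, and electrocardiogram. In Table 2 the row "Safety outcomes" carries ticks at T0 and T1 only. Outcome Measures defines T1 as "24 hours after the final treatment (T1, end point 1") and T4 as "28 days after the final treatment (T4, final end point").

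**The concern.** The boundary decides cause first and assesses cause afterwards. An event judged to belong to the pancreatitis never enters the process that asks whether the drug contributed. Yet the study drug could in principle cause or worsen the same kinds of event, and the placebo arm is there to separate drug from disease. The comparison by arm can do that only if the events are counted in both arms whatever their presumed origin. If drug-related events are filed as disease, the difference in AE rates is pulled towards zero. If the decoction prevents such complications, that benefit is missing from the safety tables too.

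The schedule is a separate matter. A team working from Table 2 and a team working from the Safety Outcomes text would collect different safety data after T1. A reader of the final report could not tell which was intended. Both points weaken the stated safety objective.

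**Working it through.** The point concerns definitions and schedule, so the check is mainly a side-by-side reading. The plan states no figure for it to reproduce.

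**1. Where else would each named complication be counted?**

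| Complication | Named capture outside AEs | What can escape |
|---|---|---|
| AKI | Renal part of the modified Marshall score, T0 to T4; SAP incidence if persistent; urea nitrogen and creatinine as safety tests | Episodes that resolve between visits |
| ARDS | Respiratory part of the modified Marshall score, T0 to T4; SAP incidence if persistent | Episodes that resolve between visits |
| Abdominal compartment syndrome | None named: the score covers the respiratory, cardiovascular and renal systems only | The diagnosis itself |

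APACHE II (to T4) and survival (at T4) add further indirect capture. None of these carries a judgement of relationship to the study drug.

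**2. How wide are the gaps between visits?** Inputs are the 48-hour course (Interventions) and the visit definitions (Outcome Measures). I take the course as the full 48 hours and the scores as measured at the visit.

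- Start of dosing to T1: 48 + 24 = 72 hours
- T1 to T2: 3 days − 24 hours = 48 hours
- T2 to T3: 7 − 3 = 4 days
- T3 to T4: 28 − 7 = 21 days

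The Introduction ties SAP to organ failure lasting at least 48 hours. No gap is shorter than 48 hours, so an episode too short to be SAP can begin and end inside any of them. Table 2 schedules no assessment during the dosing period itself.

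**3. How large is the schedule conflict?**

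- Text: T0, T1, T2, T3, T4, which is 5 times, 4 of them post-baseline.
- Table 2: T0, T1, which is 2 times, 1 of them post-baseline.
- In conflict: 4 − 1 = 3 of 4 post-baseline assessments.
- In 60 patients: 60 × 4 = 240 against 60 × 1 = 60, so 180 patient-visits are in conflict.

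The score, C-reactive protein and cytokine rows of Table 2 are ticked at all five times, and hospitalization and survival at T4. The short safety row therefore does not look like a broken table.

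**4. Why do one or two reclassified events matter?** The document gives no rate for a drug-related complication, so these rates are assumed. For 30 treated patients, the expected count is 30p and P(at least one) = 1 − (1 − p)^30.

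| Assumed rate p | Expected events | P(at least one) |
|---|---|---|
| 2% | 0.6 | 45% |
| 5% | 1.5 | 79% |
| 10% | 3.0 | 96% |

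At counts this small, filing one or two events under disease can remove most or all of the signal.

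**The case against.** The strongest reply is that the rule is narrower than it looks and that the trial counts organ failure well elsewhere. Much of that stands, and it rules out several stronger readings.

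- *All AKI, ARDS and abdominal compartment syndrome are barred from AE status.* The text does not say so. It removes only complications plainly attributable to the pancreatitis and gives these as examples. A case judged otherwise remains an AE, with causality review and serious-event reporting. What remains is that no criterion or assessor is named.
- *About 12 patients with organ failure go uncounted (20% × 60 = 12).* The 20% is the Introduction's general progression rate, not a design assumption for this intensive-care cohort. Those patients would be SAP cases, hence the primary outcome, and would be compared by arm.
- *The monitoring board would not see these events.* The Data Management and Monitoring section gives the board oversight of conduct and safety and does not limit it to events labelled AEs.
- *No safety laboratory work is done after T1 under Table 2.* Marshall scoring at T2 to T4 needs renal and respiratory data. The items really at risk are mainly liver tests, electrocardiogram, and routine blood, urine and stool tests. AE recording has no cut-off at T1.
- *Whoever assesses causality knows the arm.* The Blinding section says researchers are unaware of assignment. The Randomization section, where the recruiter opens the envelope and the project leader holds a copy of the list, raises a separate question about blinding. It does not establish who makes this assessment.

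It is also common practice to treat expected disease events differently for expedited reporting. That supports a separate reporting route, but not leaving them out of the record.

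**Conclusion.** A real defect of moderate size, in two parts.

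First, an explicit rule lets presumed cause pre-empt the causality assessment. Persistent organ failure, and dysfunction present at a visit, are still compared by arm as efficacy data. What the rule can lose is abdominal compartment syndrome, which has no other named capture, and organ failure that resolves between visits, including during dosing. Such events could end with no AE record, no drug-relationship judgement and no count by arm. This rests on reading the scores as measured at the visit. If they were taken as the worst value since the previous visit, the second loss shrinks and the first remains.

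Second, the text and Table 2 contradict each other on three of four post-baseline safety assessments. Scheduled safety assessment ends either 24 hours or 28 days after the last dose, depending on which is read. This needs no assumption.

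The documents do not show that any harm occurred or was hidden. No sample-size figure is affected.

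**What to change.** 1. Record ARDS, abdominal compartment syndrome and AKI in both arms whatever the presumed cause. They may be AEs, or a separate disease-related-event category, provided relationship to the study drug is judged blind to arm for each. Expected disease events may be handled separately for expedited reporting.
2. Tabulate them by arm with risk differences and 95% confidence intervals, and make the table available to the data and safety monitoring board. With 30 patients per arm the intervals will be wide, and the report should say so.
3. The Results section says data have been collected and are being analyzed. The events should therefore be abstracted from inpatient records by staff blind to arm, using written definitions fixed before unblinding.
4. Reconcile Table 2 with the Safety Outcomes section, and report which safety assessments were actually done at T2, T3 and T4 in each arm.
5. State how the recording category relates to the clause that links an AE to stopping the study treatment. The two need to be consistent; what the clinical rule should be is not a matter for this review.

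The cost is some chart abstraction, a longer event listing and a correction to text or table. Events that were never charted cannot be recovered, so the report should describe the abstraction as retrospective.

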### Sample Size

We will use preset sample sizes (*n*) determined using the following formula:

Where *μ*_1_ and *μ_2_* are the means of the intervention and placebo groups, respectively, and *σ* is the SD. The study aims to maintain the type I error probability (*α*) to <5% and the type II error probability (*β*) to <10%, with the *α* at .05 and the *β* at .1. To determine the sample size, we referred to literature reports in Chinese [24] on the use of DaXianXiong decoction for the treatment of AP. We used the time blood amylase took to return to normal levels to determine the clinical efficacy of the decoction. We fixed the total sample size for the study at 60. We allocated 30 patients to the intervention group and the remaining 30 to the placebo group.

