## Introduction

Acute pancreatitis (AP) is a common yet potentially fatal inflammatory disorder of the pancreas, characterized by severe abdominal pain, multi-organ dysfunction, and pancreatic necrosis. The global incidence of AP is approximately 30-40 cases per 100,000 people, with over 2000 fatalities annually [1]. Severe AP (SAP), which involves persistent organ failure lasting ≥48 hours, is the most life-threatening form of AP, with a mortality rate of 20%-40% despite significant advancements in treatment [2-4]. Approximately 20% of patients with AP progress to SAP, which is associated with severe complications such as organ failure, infections, and increased health care costs [1,5].

The pathophysiology of AP is characterized by premature activation of trypsin within the pancreatic acinar cells, triggering pancreatic autodigestion and leading to a systemic inflammatory response. This response results in systemic inflammatory response syndrome, which can progress to multi-organ dysfunction syndrome [6,7]. Although the treatment of AP is mainly supportive, including fluid resuscitation and organ support, there remains a lack of consensus on the optimal management protocols for fluid therapy [8,9], and strategies to promote gastrointestinal recovery remain limited [10].

In addition to conventional Western treatments, Chinese herbal medicines have gained attention for their potential in managing AP. Chinese herbal medicines are known for their ability to target multiple biological pathways involved in inflammation, immune response, and organ protection, offering a broader approach compared to single-target Western therapies [11,12]. DaXianXiong decoction, a traditional herbal formula used in China for over 30 years, has been reported to improve gastrointestinal symptoms and modulate inflammation. However, its clinical efficacy in preventing the progression of AP to SAP has not been conclusively demonstrated due to the lack of robust randomized controlled trials [12-14].

In light of these challenges, there is an urgent need for high-quality studies to evaluate the efficacy and safety of DaXianXiong decoction in the treatment of AP. This study aims to assess the potential of DaXianXiong decoction in preventing the progression of AP to SAP, reducing inflammatory markers, improving gastrointestinal function, and assessing safety and complications.

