### Primary Outcomes

The primary outcome of this study is the incidence of SAP, which will be calculated using the following formula:

SAP incidence (%) = (number of SAP cases/total number of patients) × 100%

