### Data Analysis

Data analyses will be performed using SPSS 24.0 software. Continuous variables with a normal distribution will be analyzed using Student *t* test, while nonnormally distributed variables will be analyzed using the Wilcoxon rank sum test. Categorical variables will be analyzed using Pearson *χ*^2^ test. Continuous variables will be presented as mean (SD), while categorical variables will be presented as percentages. Values with *P* values ≤.05 will be considered statistically significant, and all tests will be 2-sided.

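### The stated type II error of .1 belongs to time to blood-amylase normalisation, not to the primary outcome; for SAP incidence, 60 patients give power far below 90% for a halving

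*Protocol article*

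**What the plan says.** Under Sample Size, the protocol article uses a formula whose terms "are the means of the intervention and placebo groups, respectively, and *σ* is the SD", "with the *α* at .05 and the *β* at .1". The sizing variable comes from a cited report on the same decoction: "We used the time blood amylase took to return to normal levels to determine the clinical efficacy of the decoction". No means, SD or difference are given. The section continues: "We fixed the total sample size for the study at 60", split 30 and 30.

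Under Primary Outcomes: "The primary outcome of this study is the incidence of SAP", calculated as cases over patients. Data Analysis assigns categorical variables to Pearson chi-square and adds that "all tests will be 2-sided".

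Amylase is absent from the Secondary Outcomes, Other Measures, the Safety Outcomes laboratory list and the schedule in Table 2. The abstract gives a longer list of primary outcomes (SAP incidence, three severity scores, inflammation factors), and amylase is not there either. No power statement is made for SAP incidence.

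**The concern.** A sample size supports a stated error rate only for the variable, effect and test it was calculated on. Here the error rates stand at study level, the calculation behind them concerns a continuous laboratory time, and the trial's question concerns a proportion. A trial can be adequate for a large standardised difference in a continuous measure and still be weak for a difference between two proportions.

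What is at stake is the reading of the result. Someone who sees beta of .1 beside a SAP primary outcome may take a non-significant chi-square test as good evidence that the decoction does not prevent progression. If power for a plausible reduction is low, that conclusion would be unsafe.

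**Working it through.** **Inputs**
- From the plan: 30 per arm; two-sided alpha .05; beta .1; Pearson chi-square for proportions.
- Control SAP rate of 20%, from the Introduction: "Approximately 20% of patients with AP progress to SAP". This is background, not a design assumption.
- Effect of a halving: the Discussion quotes roughly this for COX-2 inhibitors. It is not a design assumption for the decoction.
- Control rates of 30%, 40% and 50%: my assumption, because enrolment is from an intensive care unit and the rate there may be higher.

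**Step 1: the plan's own figure.** The usual two-means formula is n per arm = 2(z₀.₉₇₅ + z₀.₉₀)² / (δ/σ)². Without means or SD it can only be inverted: δ/σ = (1.960 + 1.282) × √(2/30) = 0.84. So 30 per arm gives 90% power if amylase time differs by about 0.84 SD. Whether the cited report supports that cannot be seen, so 60 is neither confirmed nor refuted for amylase time.

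**Step 2: power for SAP incidence, 20% v 10%.** By normal approximation, with mean rate 0.15:

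power = Φ{[0.10 × √30 − 1.960 × √(2 × 0.15 × 0.85)] / √(0.2 × 0.8 + 0.1 × 0.9)} = Φ{(0.548 − 0.990)/0.5} = Φ(−0.884) = 18.8%.

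Summing the binomial probabilities of every 30 v 30 table that the uncorrected Pearson test rejects gives an exact 19.4%.

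**Step 3: the range, by the same two methods**

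| Control v treated | Approximate power | Exact Pearson power |
|---|---|---|
| 20% v 10% | 18.8% | 19.4% |
| 30% v 15% | 28.2% | 28.1% |
| 40% v 20% | 39.1% | 39.2% |
| 50% v 25% | 51.7% | 51.6% |
| 20% v 5% | 41.7% | 45.3% |
| 20% v 0% | 74.5% | 87.7% |

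The last exact figure can be checked by hand. With no treated cases, the test rejects from 4/30 v 0/30 upwards: z = 0.1333/√(0.0667 × 0.9333 × 2/30) = 2.07. At 3/30 v 0/30, z = 1.78. Power is therefore the chance of at least 4 cases among 30 at 20%, which is 1 − 0.123 = 0.877.

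**Step 4: scale.** For 90% power at 20% v 10%, n per arm = [1.960 × √0.255 + 1.282 × √0.25]² / 0.10² = 1.6305²/0.01 ≈ 266, or 532 in total.

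**Step 5: precision.** If 6/30 v 3/30 were observed, the difference would be −10 points with standard error √(0.16/30 + 0.09/30) = 0.0913. The 95% interval is −10 ± 17.9, or about −28 to +8 points. It includes no effect and also a reduction larger than the whole control rate.

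**The case against.** The best defence is that the Sample Size section never claims 90% power for SAP. It gives alpha and beta next to amylase time, and 60 may be correct for that variable. The Limitations section concedes a small sample, and the Discussion points to larger multicentre trials. The abstract's longer list of primary outcomes includes continuous scores, for which a two-means formula is the right type. All of this is fair. But amylase is missing from the abstract's list as well, and nothing tells the reader that the error rate does not extend to SAP incidence. That the reader will carry it over is an inference, though a natural one.

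A second objection stands and limits the claim: 19% depends on two figures that the designers did not adopt. It should never be quoted without 20% v 10% attached and the range beside it.

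Some stronger readings are tempting but not supported:
- **That amylase is not measured.** The article shows only that it is not a listed outcome or scheduled assessment; it may be measured for diagnosis.
- **That dropout was ignored.** None is stated, but the calculated n is unknown, so 60 might contain a margin. The withdrawal rule for rates above 10% is conditional, not a forecast.
- **That significance requires near elimination of SAP.** This is so only at a control rate near 20%, where 6/30 v 1/30 gives p = .044 and 6/30 v 2/30 gives p = .13. With more events, 12/30 v 5/30 already gives p = .045.

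**Conclusion.** The point holds as a mismatch between the sizing variable and the primary outcome. It does not show an arithmetic error in the figure of 60. The stated beta of .1 does not apply to SAP incidence. For a halving, power runs from about 19% to about 52% over control rates of 20% to 50%; at 20%, total prevention would still give only about 88%.

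These figures assume 30 analysed per arm, a two-sided .05 level and the uncorrected Pearson test. The control rates above 20% are assumed, and the halving is borrowed from another drug class. Power near 90% would need a much larger effect: by the normal approximation, a fall from 30% to about 1%, from 40% to about 6%, or from 50% to about 12.5%. The mismatch itself depends on none of these assumptions.

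**What to change.** Keep 60 patients. In Sample Size:
1. State that the number was derived from time to amylase normalisation, which is not a listed outcome of this trial.
2. State that beta of .1 does not apply to SAP incidence. Give the conditional power for 30 per arm: about 19% for 20% v 10%, and about 28%, 39% and 52% for a halving from 30%, 40% and 50%, with the source or assumed status of each rate.

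In Data Analysis and the trial report:

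3. Report the SAP risk difference with its 95% confidence interval alongside the chi-square test, and say that a non-significant result is not evidence of no effect.
4. Declare that item 3 was added after data collection. The Results section says the data have been collected and are being analysed, so it cannot be presented as prespecified.

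No extra patients are needed. The cost is that the stated power becomes much less favourable, and that the added estimate must be labelled as late.

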### Data and Sample Collection

To minimize selection bias, three study members will receive comprehensive training on the criteria and methods used for case collection. Detailed records of patient medication will be collected, and any interfering or contaminating factors will be excluded from the statistical analysis.

